### Exploratory outcomes

Exploratory clinical outcomes will be assessed at baseline and at the end of the four-week treatment period. Some specific outcomes will be assessed weekly in addition to pre – and post assessment, as indicated below. In this feasibility trial, the clinical outcomes will be used firstly in an exploratory manner.

#### Primary exploratory outcome

ADHD core symptoms—measured by the ADHD-IV rating scale (parent- and teacher rated) [31]. Parent ratings will be assessed at baseline, weekly, and at end of treatment. Teacher ratings will be assessed at baseline and at end of treatment.Absence from school – measured as total hours of absence reported by logbook (parents) and through direct contact with the teachers.

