#### Outcomes

### Feasibility outcomes

Feasibility outcomes will be measured at the end of the 4-week treatment period.The proportion of participants assessed for eligibility who consent to inclusion and randomizationWe will compare the number of eligible participants to the number of randomized participants. We will accept a difference above 50% (95% CI 40.2% to 59.6%). A larger difference can impose difficulties with recruitment in a future randomized trial.Compliance with the interventionWe will calculate the number of participants fulfilling treatment for both the group receiving sham and active eTNS. Compliance with treatment will be defined as completing the treatment in 70% (95% CI 58.4% to 81.6%) of the nights during the four weeks. Abruption of treatment can only be accepted if it happens within less than four nights in a row.Acceptability of the interventionThe acceptability of the intervention will be assessed using a semi-structured qualitative interview guide with predefined questions:How did you feel about administering and controlling the device?How did your child feel about receiving this type of treatment?How was it for your child to receive home-treatment with the device in addition to other strategies provided by the clinic?Did the intervention have any influence on the relationship between your child and the parents/siblings/school/friends?Completion of follow upCompletion of follow-up will be defined as completing the assessment of the primary exploratory clinical outcome at the end of the intervention. The number of participants with completed outcomes will be compared to the number of participants in total. If the number of participants completing this assessment is above 90% (95% CI 82.4% to 97.6%), this will be acceptable for a future full-size trial. If the number of participants completing the assessment is below 75%, this will introduce serious problems with the interpretation of the results.Use of concomitant treatmentAny concomitant treatment or changes in medication will be assessed for each participant and subsequently evaluated for the two groups at the end of the trial.

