### Sample size and power consideration

We will include 60 participants which corresponds to approximately 20% of the sample size needed for the full-scale randomized superiority trial. This corresponds to a power of 48% for the primary outcome (ADHD core symptoms) in this feasibility trial, indicating that the risk of type 1 error is high, and any finding thus may only be considered as exploratory.

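### School absence is scored in raw total hours with no denominator of scheduled school hours, so holidays add noise and shrink the between-arm difference

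*Protocol article*

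**What the plan says.** Under the heading Primary exploratory outcome, the protocol article lists two items. The first is ADHD core symptoms on a rating scale completed by parents and teachers: "Parent ratings will be assessed at baseline, weekly, and at end of treatment", whereas "Teacher ratings will be assessed at baseline and at end of treatment". The second is absence from school, "measured as total hours of absence reported by logbook (parents) and through direct contact with the teachers".

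The absence item does not state its counting window. The section Exploratory outcomes gives the general rule: "Exploratory clinical outcomes will be assessed at baseline and at the end of the four-week treatment period". The logbook is kept during the treatment weeks (Records of intervention; Participant timeline). I therefore read the window as each child's own four weeks. No section mentions school holidays or relates start dates to term.

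Under Feasibility outcomes, completion of follow-up means having the primary exploratory clinical outcome, in the singular, assessed at the end of the intervention. A completion share that "is above 90% (95% CI 82.4% to 97.6%), this will be acceptable for a future full-size trial". At the other end, "If the number of participants completing the assessment is below 75%, this will introduce serious problems with the interpretation of the results". The text does not say which item or which rater has to be complete.

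**The concern.** Hours absent mean little without hours at risk. Two children with the same tendency to miss school get different scores if one of them has a holiday in the window. A child with no school at all in the window gets the best possible score. Linear regression adjusted for the stratification variable (Data analysis) does not repair this, because that variable is medication use and carries no information on school hours.

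At stake is the usefulness of one of the two measures listed as primary exploratory. Raw hours from this pilot would depend on its particular mix of calendar weeks and would be a poor guide to the mean, spread or effect size to expect in the full-scale trial. Scheduled hours are also hard to recover reliably after the event, so a later analysis plan could divide by them only if they had been collected.

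A second, conditional issue follows from the loose wording of the completion criterion. If a teacher form were required, forms lost to holidays would count against a threshold on which the decision to proceed partly depends.

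**Working it through.** **1. The plan's own figure.** The interval around the 90% completion line follows from N = 60 ("We will include 60 participants which corresponds to approximately 20% of the sample size needed for the full-scale randomized superiority trial"): 0.90 ± 1.96 × √(0.90 × 0.10 / 60) = 0.90 ± 0.076, that is 82.4% to 97.6%. It reproduces.

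**2. What raw hours do to one child.** Assume 25 school hours a week, so 100 hours in four term weeks, and a child who misses 8% of school.
- Four term weeks: 0.08 × 100 = 8 hours.
- Two weeks of holiday: 0.08 × 50 = 4 hours.
- Four weeks of holiday: 0 hours, identical to perfect attendance.

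For that child, a two-week holiday changes the score as much as a true halving of absence.

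**3. What it does to the arm comparison.** Assumed inputs, none of them in the article: 25 school hours a week; mean absence 8% with a gamma spread between children (coefficient of variation 1); absence halved on active treatment; 30 children per arm; unadjusted t-test at two-sided 5%; 4,000 simulated trials per row. The expected raw difference is (0.08 − 0.04) × 25 × (4 − share affected × weeks lost).

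| Children meeting a holiday | Expected raw difference (h) | Simulated raw difference (h) | Type I error, raw hours | Power, raw hours | Power, ratio |
|---|---|---|---|---|---|
| none | −4.0 | −4.0 | 5.1% | 0.73 | 0.71 |
| 25% lose 1 week | −3.75 | −3.7 | 4.4% | 0.71 | 0.72 |
| 25% lose 2 weeks | −3.5 | −3.5 | 4.8% | 0.67 | 0.73 |
| 40% lose 2 weeks | −3.2 | −3.2 | 4.8% | 0.64 | 0.71 |
| 25% lose 3 weeks | −3.25 | −3.2 | 5.4% | 0.57 | 0.72 |

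The simulation error of a power near 0.72 is about √(0.72 × 0.28 / 4000) = 0.007. In the first row the two analyses are the same test on different scales, so the gap of 0.02 there is simulation noise. With no treatment effect, the mean raw difference is about 0 in every row. Holiday weeks explain about 2% to 13% of the between-child variance in raw hours.

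Two limits apply. The simulation treats each child's absence rate as observed exactly whatever the hours at risk, so the ratio's advantage is somewhat flattered. No simulated child loses all four weeks.

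**4. The completion criterion, only if a teacher form is required.** Above 90% of 60 means at least 55, since 54/60 = 90% exactly. Let h be the assumed share of teacher forms lost to holidays, with no other loss. Completion is then binomial (60, 1 − h).
- The chance of at least 55 is 0.92 at h = 5%, 0.44 at 10%, 0.10 at 15% and 0.01 at 20%.
- The chance of fewer than 45 (below 75%) is 0.13 at h = 20% and 0.43 at 25%.

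If only the parent rating counts, h has no effect.

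**The case against.** A reader might infer that the calendar, and not treatment, determines the result. The article does not support that. A child's place in the school year is fixed by the start date, and allocation is 1:1 in varying blocks concealed from the investigators (Randomisation and blinding). Holidays therefore fall on both arms alike in expectation, type I error holds, and for one lost week the power loss is negligible. Nor are the values wrong in themselves: the hours are counted correctly but not scaled.

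A reader might also infer that holidays threaten the completion criterion. That is the less likely reading. The Abstract names ADHD core symptoms as primary, and so does the power statement: "This corresponds to a power of 48% for the primary outcome (ADHD core symptoms) in this feasibility trial". Parent ratings do not need an open school. The calculation in step 4 is thus a reason to state which rater counts; it does not predict failure.

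It is tempting to say that absence has no baseline, because the logbook starts with treatment. That does not follow, since contact with teachers is a named second source and can cover an earlier period. Scheduling of teacher forms around term may be set out in the full protocol, and an article may leave it there.

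Finally, the clinical outcomes are exploratory throughout, and the power statement does not concern absence. All of this stands and limits the weight of the point. It does not rescue the scale, which the article states as total hours.

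**Conclusion.** The point holds as a defect of measurement. As defined, the absence outcome cannot tell full attendance from no school to attend, and it understates absence in any child whose four weeks include a holiday. The consequence is noise and attenuation, without bias towards a false effect.

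Under the assumed inputs, the raw difference falls from 4.0 hours to between 3.7 and 3.2 hours, and power from 0.73 to between 0.71 and 0.57, depending on how many children lose how many weeks. The article gives neither the share of children meeting a holiday nor the absence rate, so these figures show a range and are not estimates for this trial.

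The completion wording is a separate ambiguity. It matters only if a teacher form is counted, in which case a 10% loss of forms would make the 90% line close to a coin toss (0.44).

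The change is cheap and needs data gathered while the trial runs, so it is worth making although the outcome is exploratory.

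**What to change.** - Record scheduled school hours in the 28 treatment days through the teacher contact already planned.
- Define the outcome as hours absent divided by hours scheduled. Treat a child with zero scheduled hours as not assessable, not as 0.
- Obtain the same ratio for a stated pre-treatment period from the same teacher contact, so that the baseline assessment required for the exploratory outcomes exists for absence too.
- State under Feasibility outcomes that completion means the end-of-treatment parent-rated ADHD rating scale, in line with ADHD core symptoms as the primary outcome in the Abstract and the power statement.
- Report teacher-form completion separately. Count and describe forms missing because of holidays, and keep those children in the denominator. Removing them would raise the reported figure and hide a difficulty that the full-scale trial would also meet.

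The cost is one extra field per teacher contact, a wording change in two outcome definitions, and a few children without an assessable absence value. Start dates need not move.

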#### Secondary exploratory outcomes

Emotional liability – measured by Conners 3 Global index, Emotional liability subscale (parent – and teacher rated) [32]Quality adjusted life years—measured by the Child Health Utility instrument (CHU9D) (parent/self-rated) [33]Functional impairment – measured by the Weiss Functional Impairment Rating Scale (WFIRS) [34]Overall severity and improvement in symptoms – measured by the Clinical Global Impressions Scale (CGI) [35]Behavioural and emotional difficulties – measured by the Strengths and Difficulties Questionnaire (SDQ) (parent – and teacher rated) [36]Cognitive functioning—measured by the Behavior Ratings of Individual Executive Functions (BRIEF) (parent rated). Assessed at baseline. [37]Sleep quality—measured by The Children Sleep Habits Questionnaire (CSHQ) (parent – and teacher rated) [38]. Assessed at baseline, weekly and at end of treatment.

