## Abstract

External trigeminal nerve stimulation (eTNS) is a non-invasive technique involving external cutaneous stimulation of the trigeminal nerve. In 2019, the Monarch eTNS device was approved as a treatment for children with attention-deficit/hyperactivity disorder (ADHD). The Monarch eTNS device is designed to be applied at home, which offers a certain level of convenience but also necessitates a high degree of compliance and acceptability from the families. To assess the feasibility of – and pilot a larger randomized clinical trial investigating the Monarch eTNS device versus sham for patients aged 7 to 17 years with ADHD. We will conduct a parallel-group, sham-controlled, feasibility randomised clinical trial. We will include 60 children and adolescents (aged 7 to 17 years) diagnosed with ADHD from three clinical sites in Denmark. Patients will be randomised to 4 weeks of active versus sham eTNS. Feasibility outcomes include completion of the trial; the number of eligible participants who consent to inclusion; treatment compliance; acceptability of the intervention and completion. Adverse events will be monitored throughout the trial. Exploratory clinical outcomes include ADHD core symptoms (primary) and several secondary outcomes. Autonomic functions will be evaluated by means of heart rate variability, using a heart rate sensor. This trial will allow us to evaluate the feasibility of conducting a larger randomised clinical trial investigating the use of eTNS as a home-based, non-pharmacological intervention for children and adolescents diagnosed with ADHD.

Trial registration: ClinicalTrials.gov ID: NCT06655610. Registered 23.10.2024.

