### Participant timeline

Eligible participants will be identified by clinicians working at the respective trial sites. They will ask the families whether they are willing to be contacted by the trial researchers for further information. The trial researcher will send a letter of information and request permission to follow-up with a phone call. Following the phone call, an in-person meeting will be scheduled, in which both oral and further written information will be provided. If the families wish to participate, a second in-person meeting is scheduled. At this second meeting, informed consent is obtained as well as a standard diagnostic—and health evaluation alongside baseline assessment and HRV measurements. The child is finally included in the trial, granted they meet the inclusion criteria following the health – and diagnostic evaluation. Randomisation then commence, in which the participant is allocated to either active or sham eTNS.

They will then proceed to test the device for four weeks. Families will keep a logbook for daily reporting on how the previous night had gone by. Once a week, they will fill in an online questionnaire received by email related to the primary exploratory outcome and the reporting of any adverse events. This email will also contain questions regarding the use of the device and concomitant medication. In addition, the families will receive a weekly phone call from the trial researcher, to remind them to fill in the questionnaire and to allow the families to ask questions if needed. Families may also contact a trial researcher directly via phone throughout the trial period.

Following the four weeks, an in-person meeting is scheduled, in which the families and trial investigators meet to discuss and share their experience. During this meeting, exploratory outcomes will once again be assessed, alongside HRV measurements and the rating of any adverse events. The full participant timeline is seen in Fig. 1.

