### Data analysis

Baseline characteristics will be reported and described using descriptive statistics. Continuous outcomes will be analysed by linear regression and dichotomous outcomes will be analysed using logistic regression. In the primary analysis we will include the intention-to-treat population, i.e. all randomised participants will be included in the analysis in the group to which they were randomised, even when they have received only part of the intervention. The analyses will be adjusted for the stratification variables used in the randomisation. Before the randomisation of the last participant, we will develop and publish a detailed statistical analysis plan with a detailed description of the analyses.

Statistical analyses will be performed by two blinded statisticians presenting independent reports. Our patient population includes both treatment-naïve patients as well as those already exposed to medication. In this feasibility and pilot trial, we will assess the collective effect across all patients included. We will not investigate the effect of intervention based on medication status. Such subgroup analysis will, however, be conducted in the later, larger randomised trial. A data monitoring committee will also be included in the future, larger trial.

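### The CHU9D outcome is labelled quality adjusted life years but is a utility score taken twice; it should be named and analysed as the week-4 score, adjusted for baseline

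*Protocol article*

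**What the plan says.** Under Secondary exploratory outcomes, the protocol article names the construct and its instrument together: "Quality adjusted life years—measured by the Child Health Utility instrument (CHU9D) (parent/self-rated").

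The timing comes from the Exploratory outcomes section: "Exploratory clinical outcomes will be assessed at baseline and at the end of the four-week treatment period". It adds: "Some specific outcomes will be assessed weekly in addition to pre – and post assessment, as indicated below". In the list that follows, weekly assessment is marked for the parent-rated ADHD scale and for the sleep questionnaire, but not for CHU9D. The weekly email described under Participant timeline covers the primary exploratory outcome, adverse events, device use and concomitant medication; it does not mention CHU9D.

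Participant timeline places the baseline assessment before allocation: "Randomisation then commence, in which the participant is allocated to either active or sham eTNS". The treatment period is fixed in the Abstract: "Patients will be randomised to 4 weeks of active versus sham eTNS".

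On the model, Data analysis says: "Continuous outcomes will be analysed by linear regression and dichotomous outcomes will be analysed using logistic regression". On covariates: "The analyses will be adjusted for the stratification variables used in the randomisation". Randomisation and blinding gives one such variable, use or non-use of ADHD medication at entry. The baseline value of the outcome is not named as a covariate. The same section says "we will develop and publish a detailed statistical analysis plan with a detailed description of the analyses", to be done before the last participant is randomised.

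**The concern.** A utility is a value at a moment, and a QALY is that value summed over time. Calling a utility questionnaire the measure of QALYs therefore fixes an outcome name that does not match what is collected. A later analysis plan can supply a computation rule. If it analyses the week-4 utility, however, it departs from the named outcome. If it keeps the name and forms QALYs, it must build them from one pre-treatment and one post-treatment value.

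In that second case the pre-treatment value, which treatment cannot change, becomes part of the outcome. Unless the baseline score is also a covariate, the arm difference is diluted and chance baseline imbalance passes into it. In a pilot with 60 participants, a very small QALY difference would be hard to read as evidence on quality of life, or on whether CHU9D deserves a place in the full-scale trial.

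**Working it through.** The article gives no QALY figure, effect size, SD or power for this outcome, so there is no stated figure to reproduce. The 48% power in the sample size section concerns ADHD core symptoms and is not used here.

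**Inputs from the article.** Two CHU9D assessments, u0 (before randomisation) and u4 (week 4); a four-week period; 60 participants allocated 1:1, so 30 per arm; linear regression with the stratification variables as the only named adjustment.

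**Assumptions, not in the article.** The two-point area-under-the-curve rule; equal SDs at the two times; baseline to week-4 correlation ρ of 0.3 to 0.8; week-4 utility differences d of 0.05 and 0.10; for power, a standardised week-4 effect of 0.5, two-sided 5%, normal approximation.

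**1. Scale.** T = 28/365.25 = 0.0767 years (4/52 = 0.0769). A child in perfect health throughout accrues 0.077 QALY. T is a constant multiplier, so it changes the unit but no test, no power, and no interval relative to its effect.

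**2. Weight on the pre-treatment score.** QALY = T × (u0 + u4)/2. Randomisation balances u0 in expectation, so the expected arm difference is T × d/2, which is half of d on the utility scale.
- d = 0.05: mean utility difference 0.025; 0.025 × 0.0767 = 0.0019 QALY.
- d = 0.10: mean utility difference 0.050; 0.050 × 0.0767 = 0.0038 QALY.

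**3. Standardised effect without the baseline covariate.** The mean of the two scores has SD σ × √((1+ρ)/2), which is smaller than σ. The effect falls by a half and the SD by less, so the ratio to the week-4 standardised effect is 0.5/√((1+ρ)/2) = 1/√(2(1+ρ)). The sample size multiplier for equal power is 2(1+ρ), comparing unadjusted with unadjusted.

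| ρ | Ratio of standardised effects | Sample size multiplier | Power, week-4 score, unadjusted | Power, QALY, unadjusted | Power, either, baseline-adjusted |
|---|---|---|---|---|---|
| 0.3 | 0.62 | 2.6 | 49% | 22% | 53% |
| 0.5 | 0.58 | 3.0 | 49% | 20% | 61% |
| 0.7 | 0.54 | 3.4 | 49% | 18% | 77% |
| 0.8 | 0.53 | 3.6 | not run | not run | not run |

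**4. With baseline CHU9D as a covariate.** Given u0, the QALY is a linear function of u4. The arm coefficient and its standard error are both multiplied by T/2, so the t statistic is identical. One simulated data set of 60 confirms the algebra:
- With the stratification variable only, t was 1.39 for the week-4 score and 0.64 for the QALY.
- With the baseline score added, t was 1.90 for both. The coefficients were 0.0458 and 0.00176, and 0.0458 × (4/52)/2 = 0.00176.

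**The case against.** The strongest reply is that the averaging rule is nowhere written. The list of secondary outcomes pairs a construct with an instrument in each line, and the article defers detailed analyses to a published plan. An ordinary end-of-treatment comparison of the CHU9D score is a plausible reading. How a score is derived and which covariates enter are matters that an article normally leaves to that plan. This stands: the dilution is conditional, and the absence of a QALY rule is not itself a fault.

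A reader might infer from the label that the trial will halve any quality-of-life effect, or that the 0.077 ceiling makes the outcome uninformative. The document supports neither. The ceiling is only a unit. The loss in standardised effect needs both the assumed rule and the absence of the baseline covariate, which the article does not name but does not exclude. Nor would the QALY be noisier, because the averaged score has the smaller SD. If benefit builds up linearly over the four weeks, half the week-4 difference is the true QALY gain, so the QALY is a different estimand and not a biased one.

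Finally, the outcome is secondary and exploratory, and no feasibility criterion uses it.

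What the reply does not remove is the mismatch itself. The article fixes the outcome name, and that name is not what a utility score at week 4 measures.

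**Conclusion.** The point holds as a mislabelled outcome with a conditional analysis consequence. The label names time-accumulated utility, while the schedule delivers two point-in-time utilities, one of them before treatment.

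A literal QALY under the adjustment that the article names would show half the week-4 utility difference. Its standardised effect would be about 0.62 to 0.53 of that for the week-4 score. This rests on the two-point rule, equal SDs and a correlation of 0.3 to 0.8, all assumed. With baseline CHU9D in the model the loss of power is nil. The result is attenuation relative to week-4 utility and should not be described as bias. The impact is low.

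**What to change.** In Secondary exploratory outcomes, rename the outcome as health-related quality of life: CHU9D utility score at week 4. In the statistical analysis plan, analyse it by linear regression on arm, with baseline CHU9D and the stratification variable as covariates. Report any QALYs descriptively only, with the rule used to form them.

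The cost is one line in the outcome list and one in the analysis plan. The questionnaire and visits are unchanged, the baseline score is already collected, and QALYs can still be derived. The baseline covariate is what recovers power; the renaming makes the outcome match its measure and puts the result on a readable scale.
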